In the following, we describe the statistical methods of an observational sub-project for the secondary outcome “25(OH)D level”. This solely observational research project shall be addressed in those 228 VICTORIA trial participants who received the personalized vitamin D_3_ intervention and adhered to the trial medication (defined by taking at least 80% of the trial medication capsules), which will result in a final sample size *n* < 228. If 25(OH)D levels or log-transformed 25(OH)D levels are normally distributed (to be tested with a Shapiro-Wilks test), a linear regression model will be carried out with a continuous 25(OH)D level variable. In addition, a logistic regression model will be used with a dichotomized 25(OH)D level variable (< 50 nmol/L / ≥ 50 nmol/L) as the dependent variable.

Covariates for the linear and logistic regression model will be study center, age, sex, baseline 25(OH)D, compliance up to time of blood sampling, difference between exactly calculated and rounded supplied loading dose, number of days between last intake of trial medication and blood sampling, season at recruitment, baseline BMI, baseline waist circumference, baseline smoking, baseline physical activity, baseline physical functioning (EORTC QLQ-C30 subscale), baseline Charlson Comorbidity index, baseline frailty, baseline FACIT-F fatigue subscale, GDS-15 total score ≥ 5 points (at baseline), baseline anxiety (GAD-7 score), baseline pain (EORTC QLQ-C30 pain scale), CRC stage, time since CRC tumor surgery, stoma, concomitant use of vitamin D products (at follow-up), chemotherapy and/or radiotherapy in 9 months before trial (yes / no), chemotherapy and/or radiotherapy during trial (yes / no), concomitant use of laxatives (at baseline and/or follow-up), concomitant use of other drugs limiting vitamin D_3_ bioavailability at baseline and/or follow-up (phenytoin, barbiturates, systemic glucocorticoids, rifampicin, isoniazid, cholestyramine, orlistat, dactinomycin or systemic azole-antimycotics), nutritional vitamin D intake (at follow-up), appetite loss (at baseline and/or follow-up), sun exposure in last summer before baseline, skin type, solarium use in last 2 months before baseline, frequency of diarrhea (at baseline and/or follow-up), vitamin D binding protein levels and single nucleotide polymorphisms (SNPs) previously shown to be associated with low 25(OH)D levels. If appropriate, missing covariate values will be imputed with multiple imputation.

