Mean 25(OH)D levels and proportions of study participants with 25(OH)D levels < 50 nmol/L will be presented distinctly for factors that were statistically significant (*p* < 0.05) determinants of achieved 25(OH)D levels.

The analyses will be carried out both for the 25(OH)D measurement from day 12–21 (end of loading dose consumption) and for the 25(OH)D measurement from week 13–16 (end of maintenance dose consumption).

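### In the exploratory sub-project, the day 12–21 25(OH)D model uses covariates taken wholly or partly at week 13–16, so they can include exposures that began after the outcome

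*Protocol article*

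**What the plan says.** All of this is in the Protocol article. Under Statistical methods, the exploratory sub-project on determinants of the achieved 25(OH)D level gives a single covariate list for its linear and logistic models. Most entries carry a time label. Seven of them are not confined to the time before the early blood sample:

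- Follow-up only: "concomitant use of vitamin D products (at follow-up" and "nutritional vitamin D intake (at follow-up".
- Whole trial: "chemotherapy and/or radiotherapy during trial (yes / no".
- Baseline, follow-up or both: "concomitant use of laxatives (at baseline and/or follow-up", "concomitant use of other drugs limiting vitamin D_3_ bioavailability at baseline and/or follow-up", "appetite loss (at baseline and/or follow-up" and "frequency of diarrhea (at baseline and/or follow-up".

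The same text then says: "The analyses will be carried out both for the 25(OH)D measurement from day 12–21 (end of loading dose consumption", and goes on to the week 13–16 measurement. It does not change the list between the two. Factors with p < 0.05 are to be presented as determinants of the achieved level.

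The Questionnaires section provides for a questionnaire at baseline and another in weeks 13 to 16, with none in between. Table 3 marks concomitant medication and the assessment of cancer treatment at screening and at week 13–16. It marks the query on self-medication with vitamin D at week 13–16 only.

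**The concern.** The day 12–21 model asks what governs the response to the loading dose. A product, drug course, treatment cycle or symptom that began after the sample cannot have influenced the level in it. If such an exposure enters the early model, some participants are counted as exposed who were not exposed at the relevant time. True early associations then tend to shrink, and a factor may be reported as a determinant although it followed the outcome.

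The setting also changes between the two times. The day 12–21 sample is taken at the end of the inpatient stay, and the week 13–16 data come from outpatients. Diet, medication and symptoms at the second time are therefore an uncertain guide to the first.

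The plan does attend to timing elsewhere: compliance is counted only up to the blood sample, and many other covariates are baseline values. The seven listed here have no such limit.

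**Working it through.** The sub-project gives no effect size or precision that could be reproduced. Its only figure is a sample below 228, the verum half of those randomized (456 / 2 = 228). The check concerns timing and the analysis set.

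**1. Which covariates are affected.** From the list: 2 follow-up only + 1 whole-trial + 4 baseline, follow-up or both = 7.

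**2. What follow-up means.** The sub-project text does not define it. The Questionnaires section and Table 3 leave week 13–16 as the only time after baseline at which these items are collected.

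**3. Distance from the early outcome.** Week w covers days 7(w − 1) + 1 to 7w.

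- Week 13 begins on day 7 × 12 + 1 = 85, and week 16 ends on day 7 × 16 = 112.
- Shortest gap: 85 − 21 = 64 days (64 / 7 = 9.1 weeks).
- Longest gap: 112 − 12 = 100 days (100 / 7 = 14.3 weeks).

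**4. Who is in the analysis set.** The sub-project keeps only verum participants who took at least 80% of their capsules. For someone who stops at day 21:

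- With one capsule a day for 84 days: 21 / 84 = 25% taken.
- With the maximum loading dose (420,000 / 20,000 = 21 capsules in 11 days, then one a day): taken by day 21, 21 + 10 = 31; planned total, 21 + 73 = 94; 31 / 94 = 33%.

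To reach 80%, the first schedule needs 0.8 × 84 = 67.2, so 68 capsules, reached on day 68. The second needs 0.8 × 94 = 75.2, so 76 capsules, of which 76 − 21 = 55 are maintenance capsules, reached on day 11 + 55 = 66. Anyone who leaves soon after visit 2 is therefore outside the set.

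**5. What data exist for an early version.** Table 3 shows no record of concomitant medication at visit 2, and there is no questionnaire then. The four mixed covariates have a baseline value but no visit 2 value. The article does not say whether dates of chemotherapy or radiotherapy are collected. Pre-trial chemotherapy or radiotherapy is a separate covariate on the same list.

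**The case against.** The strongest reply is that four of the seven covariates do have a baseline value. How their mixed wording is coded at each outcome time could be settled in a fuller analysis plan. A follow-up report may also reflect a lasting habit or treatment and so serve as a rough proxy for the earlier period. This has some force: those four are open to contamination rather than bound to it. It does not help the two follow-up-only items or the whole-trial one, and the article states one list for both times.

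Three stronger readings might be inferred, and the documents do not support them.

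- *Drop-outs would lack these covariates in the early model.* Applying the 10% drop-out rate to 228 gives about 23 people. But the 80% capsule rule removes early leavers, as shown above, and repeated mail and telephone contact limits missing questionnaires among those who stay.
- *Most of what the follow-up items describe lies after the early sample.* Of the 84 treatment days, (84 − 21) / 84 = 75% to (84 − 12) / 84 = 86% are still to come. That would be the share described only if the items looked back over the whole treatment period. A 12-week recall window is stated for infection frequency but not for these items.
- *The early model will produce many false determinants.* Sites are shielded from post-baseline 25(OH)D results, and participants learn their latest result only after their trial ends. The early level is therefore unlikely to drive later behaviour. Dilution is the more likely harm.

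It is also fair to say that the sub-project is labelled exploratory and observational.

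**Conclusion.** The point holds in a limited form. As written, the day 12–21 model includes two covariates recorded only 64 to 100 days after its outcome, one that runs over the whole trial, and four that may include follow-up values. Early exposure is misclassified, mainly towards diluted associations, and a later exposure could be named a determinant. The size of the bias cannot be calculated, because the article gives neither recall windows nor exposure frequencies.

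The conclusion assumes that follow-up means week 13–16, the only reading that the schedule allows. Setting the drop-out argument aside assumes that the 80% rule refers to all planned capsules, as the wording suggests.

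The week 13–16 model does not have this mismatch of 64 to 100 days. The primary endpoint, the sample size, the randomized comparisons and the one-sample test against 50 nmol/L are untouched. This is a minor correction.

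**What to change.** State two covariate lists in the sub-project.

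- **Day 12–21:** use the baseline versions of laxatives, interacting drugs, appetite loss and diarrhea. Count chemotherapy or radiotherapy only up to the blood sample if treatment dates allow; otherwise use only the pre-trial variable. Leave out the follow-up-only items on vitamin D products and nutritional intake, or keep them solely in a sensitivity model that calls them proxies.
- **Week 13–16:** keep the current list.

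Make the change before the planned interim analysis, which includes this sub-project. It alters analysis wording and needs no new data, provided that the pre-trial treatment variable is used where dates are lacking. The price is that the main early model loses its only control for additional vitamin D intake, imperfect as that control is. The labelled sensitivity model would show whether this matters.

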#### *Intervention arm*

The vitamin D_3_ treatment consists of a personalized loading dose, followed by a daily maintenance dose of 2000 IU. Several clinical trials have highlighted that 25(OH)D levels, achieved by vitamin D_3_ intake, strongly depend on a person’s 25(OH)D level and weight at baseline [29–31]. In order to provide the trial participants with a sufficient vitamin D_3_ dose, an equation to calculate individual loading doses is applied. The equation includes the baseline 25(OH)D level and body mass index (BMI) [31]:

Loading dose = 165 * BMI [kg/m^2^] * (70 – baseline 25(OH)D level [nmol/L]).

The equation by Jansen et al. was developed to increase 25(OH)D levels to 80 nmol/L, which is slightly above the generally accepted optimal level of 75 nmol/L [32]. In order to avoid non-physiological high doses of vitamin D_3_, the loading dose will be distributed in daily doses of 20,000 IU, which resembles the maximum amount of vitamin D_3_ that can be naturally produced in the skin by sunbathing in a swimsuit on a summer day [33]. The reasons for this are not safety concerns but mechanistic considerations regarding the vitamin D_3_ metabolism: Unbound vitamin D_3_ in the serum is of major importance for effective vitamin D activity [34, 35]. Its bioavailability in turn is higher when doses are given on a daily basis while avoiding single high doses [34, 35].

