As a sensitivity analysis, a linear regression model will be carried out with FACIT-F fatigue subscale as the dependent variable and treatment group as the independent variable. The linear regression model will be adjusted for all variables named in the subgroup analysis while using some variables continuously instead of categorically (age, hemoglobin levels at screening, 25(OH)D levels at screening, BMI at screening, FACIT-F fatigue subscale at screening, insomnia scale at follow-up and pain scale at follow-up). If appropriate, missing covariate values will be imputed with multiple imputation.

All secondary endpoints with a continuous scale will be analyzed with the same statistical methods as described for the primary endpoint. All dichotomous secondary endpoints will be tested with a Chi^2^ test. AEs will be analyzed with descriptive statistics including frequencies of SAEs.

Lastly, the success of the personalized vitamin D_3_ intervention in raising the serum 25(OH)D level will be evaluated in the intervention group at trial day 12–21. Furthermore, the success of the maintenance dose to maintain sufficient vitamin D status in the intervention group will be evaluated in trial week 13–16. To be successful, the mean 25(OH)D levels in the group with personalized vitamin D_3_ intervention should be higher than 50 nmol/L. This translates into the following test hypotheses:
H_0_: Mean 25(OH)D_personalized intervention_ ≤ 50 nmol/LH_1_: Mean 25(OH)D_personalized intervention_ > 50 nmol/L

To test these hypotheses, we will conduct a one-sample t-test on the mean 25(OH)D levels at a one-sided significance level of 0.025. 25(OH)D levels may be log-transformed if this improves the approximation of a normal distribution (to be tested with a Shapiro-Wilks test).

*Exploratory sub-project: “Determinants of the achieved 25(OH)D levels by the personalized vitamin D*_*3*_*intervention”*

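### The sub-project's display of achieved 25(OH)D is filtered on p < 0.05, so baseline 25(OH)D and BMI would usually be missing from it at day 12–21 if the loading-dose equation works

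*Protocol article*

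**What the plan says.** All places are in the Protocol article.

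- **Intervention arm.** The loading dose is personalized because achieved levels "strongly depend on a person’s 25(OH)D level and weight at baseline". The equation uses baseline 25(OH)D and BMI and was developed to reach 80 nmol/L. The maintenance dose is the same for everyone.
- **Statistical methods, success of the intervention.** Success is judged on one figure for the whole arm: "the mean 25(OH)D levels in the group with personalized vitamin D_3_ intervention should be higher than 50 nmol/L".
- **Statistical methods, exploratory sub-project.** Adherent verum patients are analysed, "which will result in a final sample size *n* < 228". A linear model is fitted if normality is met. For the second model the text says "In addition, a logistic regression model will be used with a dichotomized 25(OH)D level variable". The covariate list is long. It opens with "Covariates for the linear and logistic regression model will be study center, age, sex, baseline 25(OH)D, compliance up to time of blood sampling" and later has "season at recruitment, baseline BMI, baseline waist circumference, baseline smoking".
- **Same section, display rule.** Mean 25(OH)D levels and proportions below 50 nmol/L "will be presented distinctly for factors that were statistically significant (*p* < 0.05) determinants of achieved 25(OH)D levels", at day 12–21 and at week 13–16.
- **Interim analyses.** The sub-project is also run on the first 228 participants (both arms) with a week 13–16 blood sample.

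**The concern.** The Discussion presents the personalized loading dose as a novel feature of the trial. A natural question for the sub-project is whether that dose evens out achieved levels across baseline 25(OH)D and BMI, the two inputs of the equation. If it does, neither factor should be a significant determinant after loading, and the display rule then leaves both out. The reader would not see the similar means and similar proportions below 50 nmol/L across strata that would support personalization. The pooled mean test cannot supply them, because an arm mean above 50 nmol/L is compatible with one stratum lying below it.

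Two further problems follow from using p < 0.05 as the gate. A factor can miss the threshold because the model is imprecise, so absence from the display does not mean that the dependence has gone. And a factor that only just passes will, on average, be shown with too large a difference.

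**Working it through.** **1. Plan's own figures.** With SD 10.8, difference 3, two-sided 0.05 and 80% power: 2 × (1.960 + 0.842)² × (10.8/3)² ≈ 203.4, or 204 per arm. The t-based solution is 204.4, rounded up to the stated 205. Then 410/0.9 = 455.6, or 456 randomized and 228 per arm. These reproduce. The article gives no precision figure for the sub-project.

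**2. Assumptions (not in the documents).** 10% loss to non-adherence or missing samples, so 228 × 0.9 ≈ 205 patients; 40 model terms; residual SD of 25(OH)D 20 nmol/L; a BMI–waist correlation of 0.87, so VIF = 1/(1 − 0.87²) ≈ 4. At interim, 228/2 = 114 verum patients, and 114 × 0.9 ≈ 103.

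**3. How often the two factors are missing if the equation works.** With no residual dependence each passes at the nominal 5%. In 2,000 simulated regressions at n = 205 the pass rates were 3.9% (baseline 25(OH)D) and 5.1% (BMI). Each is therefore absent about 95% of the time per model and time point. The article does not say which model's p-value counts. If either suffices, the nominal pass rate is at most 2 × 5% = 10% per time point, so each factor is still absent at least about 90% of the time.

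**4. What non-significance is worth.** The SE of a standardized slope is √(VIF/df), with df = 205 − 40 − 1 = 164. For VIF 1 it is √(1/164) = 0.078; for VIF 4 it is √(4/164) = 0.156. Among slopes that pass, the exaggeration factor is the mean absolute estimate divided by the true value.

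| True slope (SD per SD) | VIF 1: power | VIF 1: exaggeration | VIF 4: power | VIF 4: exaggeration |
|---|---|---|---|---|
| 0.1 | 0.24 | 2.00 | 0.10 | 3.80 |
| 0.2 | 0.72 | 1.18 | 0.24 | 2.00 |
| 0.3 | 0.97 | 1.02 | 0.48 | 1.43 |

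A true slope of 0.1 is missed 76% of the time at VIF 1. At VIF 4, the assumed position of BMI beside waist circumference, a slope of 0.2 is missed 76% of the time (73% in simulation).

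**5. Interim run (n about 103, VIF 1).** df = 103 − 40 − 1 = 62 and SE = √(1/62) = 0.127. The exaggeration factors are 3.15, 1.69 and 1.25 for slopes of 0.1, 0.2 and 0.3.

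**6. Crude group differences, closer to what would be displayed.** Baseline 25(OH)D was split at its median in the simulation, and the difference was shown only when its regression slope passed p < 0.05.

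| Slope | n = 205: true → shown (nmol/L) | n = 103: true → shown (nmol/L) |
|---|---|---|
| 0.1 | 3.2 → 5.8 | 3.2 → 7.2 |
| 0.2 | 6.4 → 7.3 | 6.3 → 8.9 |
| 0.3 | 9.6 → 9.7 | 9.5 → 11.0 |

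**7. What an interval would show.** At n = 205 the 95% CI half-width is about 1.97 × 0.078 = 0.15 SD per SD for baseline 25(OH)D, or 0.15 × 20 ≈ 3 nmol/L per SD. For BMI at VIF 4 it is 1.97 × 0.156 = 0.31, or about 6 nmol/L per SD. This lets the reader judge compensation, and a missing row does not.

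**The case against.** The display sentence does not contain the word only. It describes one descriptive summary after two prespecified regressions that both include baseline 25(OH)D and BMI, and nothing says that their coefficients are withheld when non-significant. A near-zero coefficient with its CI would be the evidence wanted, and a condensed article may leave the layout of regression tables to a fuller document. This stands. A reader might infer that the evidence for personalization will go unreported; the text supports only its absence from the by-factor means and proportions.

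A reader might also infer that no other analysis can show the pattern. That is not established. The continuous secondary endpoints, which include 25(OH)D, follow the methods of the primary endpoint. If those include the a priori subgroups by screening 25(OH)D and BMI, some of the pattern would appear there. The text leaves this open, and such subgroups would compare treatments at a single cut-off, not describe achieved levels among adherent verum patients.

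The argument about compensation applies to day 12–21. By week 13–16 all patients have been on a fixed maintenance dose, so dependence on body size could return even if loading worked, and the rule would then tend to display it.

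Nor is every displayed effect exaggerated: at n = 205 a strong determinant is shown almost unbiased (9.6 → 9.7 nmol/L). Miss rates from a simple unadjusted binary factor should not be carried over to BMI or baseline 25(OH)D entered as continuous terms. At VIF 1 a slope of 0.2 is missed only 28% of the time.

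**Conclusion.** The point holds as a low-severity flaw in an exploratory analysis. The rule tends to remove from the display the two factors on which the dose is built, in about 95% of cases per model at day 12–21 if the equation fully compensates. That absence cannot be read as success, because moderate residual slopes are often missed, above all for BMI with waist circumference in the same model. Displayed differences are too large on average for weak determinants (by a factor of about 1.8 at a true 3.2 nmol/L, since 5.8/3.2 = 1.8) and more so at interim; for strong determinants the excess is negligible.

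The sizes rest on the assumed 205 patients (103 at interim), 40 terms, SD 20 nmol/L and VIF 4. The 5% pass rate needs only valid tests. The fatigue analysis and the test of the arm mean against 50 nmol/L do not use the filter and are unaffected.

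**What to change.** Change the display rule in the sub-project as follows.

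1. Present mean 25(OH)D and the proportion below 50 nmol/L, with 95% CIs, by baseline 25(OH)D and by BMI at both time points, whatever the p-value.
2. Report estimates with 95% CIs for all other prespecified covariates.
3. Judge compensation by the loading equation from whether the day 12–21 CIs for the baseline 25(OH)D and BMI slopes exclude a gradient that would matter, not from p < 0.05.
4. Read week 13–16 separately, because maintenance is not personalized.

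The cost is a change of wording and a longer results table. No new data are needed.

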#### *Interim analyses*

No interim analyses are planned for the primary outcome FACIT-F fatigue subscale in trial week 13–16 and the following ones have no implications for the ongoing of the trial.

Interim analyses are planned with the first half of the intended final sample size to be randomized, i.e. 228 study participants with available blood samples from week 13–16. The analyses will be focused on 25(OH)D-related secondary outcomes, all safety parameters and for the exploratory sub-project: “Determinants of the achieved 25(OH)D levels by the personalized vitamin D_3_ intervention”.

## Discussion

The present trial is by far the largest to address the efficacy of vitamin D_3_ supplementation on fatigue as a primary outcome and the first to be conducted in non-metastatic CRC patients in whom the prevalence of vitamin D insufficiency/deficiency and fatigue are particularly high [4]. Its novel methodological aspects are the use of season-adapted serum 25(OH)D cut-offs to determine suitability for inclusion in the trial and a personalized vitamin D_3_ loading dose over several days, thereby avoiding a single non-physiological high dose. The use of placebo has been considered to be ethically justifiable in CRC patients where vitamin D insufficiency is commonly found but usually neither diagnosed nor treated. Participants in the intervention group might benefit from the treatment of their vitamin D deficiency by prevention or reduction of fatigue symptoms. Daily administered oral vitamin D_3_ treatment in the proposed doses is considered acceptable for CRC patients concerning the expected benefit-risk profile.

The results of the trial are highly relevant for practice: Firstly, the trial population is representative of non-metastatic CRC patients suffering from vitamin D insufficiency/deficiency and attending a German rehabilitation clinic. The in−/exclusion criteria are kept to a necessary minimum to ensure generalizability. Secondly, vitamin D_3_ is not patented and available on the market at low cost. Consequently, the trial could be used as a base for a policy change offering a cost-effective screening and treatment of vitamin D deficiency to CRC patients in rehabilitation clinics. This would not only have a major impact on the therapy of fatigue and QoL but possibly on the survival of this population as well [40].

The choices of the trial intervention and the trial end-points have been discussed with the *Deutsche ILCO e.V.* (a patient advocacy group for CRC). We were assured that fatigue is a highly patient-relevant outcome for CRC patients within months to years after curative treatment and represents an unmet need, which complies with reports in the scientific literature [41, 42].

